# Effects of Traditional Chinese Exercise Yijinjing on Disability and Muscle Strength Among Patients With Chronic Low Back Pain: Protocol for a Randomized Controlled Trial

**DOI:** 10.2196/67557

**Published:** 2025-05-07

**Keywords:** chronic low back pain, traditional Chinese exercise, Yijinjing, muscle strength, randomized controlled trial

## Abstract

**Background:**

Chronic low back pain (CLBP) is a common public health problem. Progressive loss of muscle strength leads to long-term chronic pain and disability. Yijinjing exercises, an ancient therapy dating back thousands of years, are widely used in China to treat low back pain. However, little is known about its benefits and scientific evidence for back extensor strength. This trial aimed to assess the efficacy of Yijinjing on disability and dorsal extensor strength in patients with CLBP.

**Objective:**

We present a randomized controlled study to evaluate the efficacy of the traditional Chinese exercise Yijinjing on disability and back extensor strength in patients with CLBP.

**Methods:**

This is a 2-arm, parallel-design, assessor-blinded, and analyst-blinded randomized controlled trial. The 106 participants with CLBP who were recruited will first receive basic traditional Chinese manual therapy to help relieve their physical discomfort. Second, they will be randomly divided into a Yijinjing group (n=53) and a control group with functional exercises (n=53) at a ratio of 1:1. The interventions for both groups will be carried out twice a week for 4 weeks. Patients in both groups will be followed up at 1 and 3 months after the intervention. The primary outcome is disability (measured by the Oswestry Disability Index). The secondary outcomes included pain intensity (assessed by the Numerical Rating Scale), data from isokinetic dynamometry, flexibility (assessed by the fingertip-to-floor test), mood (evaluated by the Pain Catastrophizing Scale and Fear Avoidance Beliefs Questionnaire), and quality of life (measured by the EQ-5D-5L). All adverse effects will be assessed using the Treatment Emerging Symptoms Scale, and data will be analyzed using an intention-to-treat analysis.

**Results:**

The trial was funded in December 2023. The Institutional Ethics Committee of Yueyang Hospital of Integrative Medicine, Shanghai University of Traditional Chinese Medicine, approved this study. The first patient was enrolled in February 2024, and as of August 2024, a total of 106 participants have been recruited. Data analysis has not yet begun and is expected to be published in January 2025. The protocol has been registered with the Chinese Clinical Trial Registry (ChiCTR2400081105).

**Conclusions:**

If this trial proves effective, it will guide the setup of a randomized controlled trial to demonstrate whether traditional Chinese exercise Yijinjing improves disability in patients with CLBP and is more effective than usual stretching exercises.

**Trial Registration:**

Chinese Clinical Trial Registry ChiCTR2400081105; https://www.chictr.org.cn/showprojEN.html?proj=214425

**International Registered Report Identifier (IRRID):**

DERR1-10.2196/67557

## Introduction

Chronic low back pain (CLBP, Multimedia Appendix 1) is the second most common reason for medical consultations worldwide. It leads to disability and loss of muscle strength and affects quality of life and work [1,2]. This results in a high health care burden and indirect social costs [3]. Although most patients with CLBP recover quickly with a variety of medications, including nonsteroidal anti-inflammatory drugs, muscle relaxants, and opioids, 20%-30% still fail to improve function sufficiently, endure diminished lower back muscle strength, and even experience pain recurrence or worsening [4,5]. Therefore, active research into complementary therapies for CLBP to improve function, increase muscle strength, and reduce recurrence is important.

In China, many people with CLBP voluntarily seek traditional Chinese manual therapy (TCMT). It provides short-term pain relief. However, the recurrence rate is high. This is likely because TCMT is a passive therapy with limited effects on muscle strength recovery [6]. As popular sports become more influential in society, increasing attention is being given to the impact of physical activity on mental health [7,8]. Physical activity plays an important role in CLBP [9-11]. Nonpharmacological treatments recommended for CLBP include exercise therapy, yoga, and back school [5]. Among these treatments, yoga is widely recommended for patients with CLBP, but there are many types [12,13]. It is too difficult to choose for patients with CLBP. In China, many patients with CLBP voluntarily seek Yijinjing, which has a long history as an ancient traditional Chinese exercise therapy that originated in 221 BC. It combines positive thinking with deep contemplation, fluid movement, deep breathing, and relaxation techniques to promote the circulation of vital energy (or Qi) throughout the body [14]. It is considered a multifaceted intervention that includes physical, mental, social, emotional, spiritual, and cognitive-behavioral aspects. Our previous studies demonstrated that Yijinjing can significantly reduce the disability and pain associated with osteoarthritis and increase the effects on mood and muscle strength [15,16]. However, its potential benefits for CLBP remain less well studied [17]. Therefore, if proven beneficial for CLBP, Yijinjing could provide another exercise therapy option for the large number of Chinese residents enduring CLBP.

This RCT compared Yijinjing with self-stretching exercises (SSE), such as yoga. We hypothesized that patients randomized to Yijinjing would have greater short- and long-term improvements in functional disability, back muscle strength, and other outcomes associated with CLBP compared to those randomized to stretching training. We will explore the correlation between these outcomes.

## Methods

### Study Design

This study is a single-center, assessor-blinded and analyst-blinded prospective randomized controlled trial with 2 parallel arms. This study was conducted in Shanghai, China, at Yueyang Hospital of Integrated Traditional Chinese and Western Medicine affiliated with Shanghai University of Traditional Chinese Medicine. All eligible participants will be recruited. First, they receive basic TCMT to help relieve their physical discomfort. Second, they will be randomly assigned to the Yijinjing and SSE groups at a 1:1 ratio after receiving TCMT. This trial protocol was approved by the Ethics Committee of Yueyang Hospital of Integrated Traditional Chinese and Western Medicine affiliated with the Shanghai University of Traditional Chinese Medicine (project number 2023-203). It is registered with the Chinese Clinical Trial Registry (ChiCTR2400081105). All patients signed a written informed consent form. The intervention will be administered twice per week for 1 month. The outcome assignment and statistical analyses will be completed blindly. The trial flowchart and research design are shown in Figure 1. The protocol for this study will adhere to rigorous standards as outlined by the Declaration of Helsinki, the CONSORT (Consolidated Standards of Reporting Trials) [18], and the SPIRIT (Standard Protocol Items: Recommendations for Interventional Trials) [19] guidelines. This commitment ensures the ethical and transparent conduct of our trial.

**Figure 1 figure1:**
[figure not shown]
Flowchart of the study procedure.

### Outcome

This study will evaluate the Oswestry Disability Index (ODI), Numerical Rating Scale (NRS), Pain Catastrophizing Scale (PCS), Fear Avoidance Beliefs Questionnaire (FABQ), EQ-5D-5L, the Flexibility Test, and the muscle strength test in the fourth week of the experiment. Furthermore, the results of the ODI, NRS, PCS, FABQ, and EQ-5D-5L will be followed up at the 8th and 16th weeks. The schedule of evaluations is outlined in Table 1 (Multimedia Appendix 2).

**Table 1 table1:** Schedule of enrollment, intervention, and outcome measures.

Enrollment	Screening and allocation	Treatment period		Follow-up period	
	Week 0	Week 1-3	Week 4	Week 8	Week 16
Inclusion or exclusion criteria	✓	—^a^	—	—	—
Informed consent form	✓	—	—	—	—
Medical history	✓	—	—	—	—
Physical examination	✓	—	—	—	—
Eligibility for study	✓	—	—	—	—
Baseline characteristics	✓	—	—	—	—
C-spine x-ray	✓	—	—	—	—
Allocation	✓	—	—	—	—
Intervention	—	—	—	—	—
Yijinjing^b^	—	—	—	—	—
SSE^b,c^	—	—	—	—	—
Outcomes	—	—	—	—	—
ODI^d^	✓	—	✓	✓	✓
NRS^e^	✓	—	✓	✓	✓
PCS^f^	✓	—	✓	✓	✓
FABQ^g^	✓	—	✓	✓	✓
EQ-5D-5L	✓	—	✓	✓	✓
Flexibility test	✓	—	✓	—	—
Muscle strength test	✓	—	✓	—	—

^a^Not applicable.

^b^Two times a week from weeks 1-4.

^c^SSE: self-stretching exercises.

^d^ODI: Oswestry Disability Index.

^e^NRS: Numeric Rating Scale.

^f^PCS: Pain Catastrophizing Scale.

^g^FABQ: Fear Avoidance Beliefs Questionnaire.

### Participant Recruitment

Recruitment advertisements for this trial will be posted in the outpatient clinics of Yueyang Hospital and the Traditional Chinese Manipulative Therapy Department. Additionally, we will advertise through WeChat, which is the most widely used social media platform in China, to ensure easy access to interested participants. Potential participants will contact this study’s team by phone or WeChat. One of the researchers will verbally explain this study’s protocol and eligibility criteria to the potential participants and assess their eligibility over the phone after they provide verbal consent. Eligible potential participants will receive participant instructions and informed consent via WeChat or email, which will allow them at least 24 hours to review the documents. If the potential participant still expressed interest in participating and met the eligibility requirements, then they were invited to attend a baseline meeting. At baseline, one of our researchers will review this study’s protocol, reconfirm participant eligibility, and obtain written informed consent. Additionally, a baseline assessment will be conducted during the meeting, which will include all primary and secondary outcomes and demographic information. Thereafter, patients will be randomized.

### Sample Size Calculation

The calculations are based on hypothetical changes in the ODI at week 6. We use the results of a randomized controlled trial to formulate the intended effect. We hypothesize a 3.57-point improvement on the ODI scale in the Yijinjing group compared to the control group [20]. The sample size for each group provided 90% power, and these differences were detected using PASS software (version 15.0.5; NCSS, LLC) at a 2-sided significance level of .05. Considering an expected dropout rate of 20%, a total of 106 patients are required for this study.

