### Statistical Analysis

In this study, the principle of intentionality analysis will be used to analyze the data. The safety analysis set will be used to analyze the safety of this study. A statistician who is unaware of the group assignments will use SPSS statistical software (version 26.0; IBM Corp) to analyze the data. All effects will be estimated using 95% CIs, and all the statistical tests will be 2-sided. A *P* value less than .05 indicated statistical significance.

Continuous variables are presented as the mean (SD) if they follow a normal distribution; otherwise, they are presented as medians and quartiles. Categorical variables are presented as percentages. Primary outcomes will be assessed using analysis of covariance adjusted for baseline. For other secondary outcomes, *t*-tests or Wilcoxon rank-sum tests will be used.

Repeated outcomes over time will be compared using linear mixed-effects models with the following fixed effects: (1) time points (categorical), (2) intervention group, (3) time-by-group interaction, and (4) baseline measurement as a covariate. Random intercepts for participant ID will be included to account for within-subject correlations. Additional adjustments will be made for prespecified covariates, including age, gender, and study site (if multicenter). Bonferroni correction was used for multiple comparisons across time points.

Missing data will be replaced according to the principle of carry-over of last observations. Missing values for dropout cases will be imputed using either the last observation carried forward method if the dropout rate is below 5% or the multiple imputation method for a dropout rate of 5% or higher. If the attrition rate exceeds 10%, we use per-protocol analysis to ensure the reliability of this study.

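### The trial is sized on ODI at week 6, when no ODI is measured, and no scheduled visit is named primary, so it is unclear whether the primary test is one contrast at .05 or three at about .0167

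*Protocol article*

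**What the plan says.** **Sizing.** The Sample Size Calculation section says: "The calculations are based on hypothetical changes in the ODI at week 6". The effect is given as follows: "We hypothesize a 3.57-point improvement on the ODI scale in the Yijinjing group compared to the control group". Power is 90%, the test is two-sided at .05, dropout is 20% and the total is 106. No standard deviation is given.

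**Schedule.** The Outcome section lists ODI among the measures taken at week 4, in a sentence that ends "the muscle strength test in the fourth week of the experiment". It then says that ODI and the other questionnaires "will be followed up at the 8th and 16th weeks". Table 1 agrees, with ODI at weeks 0, 4, 8 and 16. The Abstract fits too: four weeks of intervention, then follow-up one and three months later.

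**Endpoint.** The Abstract says: "The primary outcome is disability (measured by the Oswestry Disability Index". Neither it nor the Primary Outcome section attaches a visit. The hypothesis in the Introduction is of "greater short- and long-term improvements in functional disability", which singles out no time point.

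**Analysis.** The Statistical Analysis section says: "Primary outcomes will be assessed using analysis of covariance adjusted for baseline". The next paragraph gives a linear mixed model for outcomes measured repeatedly, which describes ODI, and adds: "Bonferroni correction was used for multiple comparisons across time points".

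**The concern.** Week 6 matches no scheduled ODI assessment, and it is not the end of the intervention. It is also the only week that the article ties to the size of the primary effect. A reader therefore cannot infer the primary visit from the sample size section, and no other section names it.

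An ANCOVA of this kind compares the groups on one post-baseline value, and here there are three to choose from. Two readings remain. In one, the primary test is a single ANCOVA contrast at .05, at a visit not yet named. In the other, the primary question is answered at all three visits under the Bonferroni rule. The sample size uses an unadjusted .05, which fits only the first.

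What is at stake is the trial's one confirmatory test. If the visit stays open, it can be chosen after the results are seen. Participants are not blinded and ODI is a questionnaire, so such a choice would be hard to defend.

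**Working it through.** **1. The visits side by side**

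| Source in the protocol article | ODI time point |
|---|---|
| Sample Size Calculation | week 6 |
| Outcome section and Table 1 | weeks 0, 4, 8, 16 |
| Abstract: end of intervention; 1 and 3 months later | weeks 4; 8 and 16 |
| Abstract and Primary Outcome section: definition of endpoint | none given |
| ANCOVA sentence, Statistical Analysis | none given |

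Week 6 appears only in the first row.

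**2. The stated total**

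The total of 106 cannot be reproduced from the stated inputs, because no standard deviation is given. It can only be inverted.

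- 106 in total is 53 per arm. With 20% dropout, 42 evaluable per arm gives 42 / 0.8 = 52.5, rounded up to 53.
- The normal approximation is n = 2(z₀.₉₇₅ + z₀.₉₀)² SD² / Δ², so SD = Δ / (1.960 + 1.282) × √(n/2).
- With Δ = 3.57 and n = 42: 3.57 / 3.2415 × √21 = 5.05. The t-test version gives 4.99.
- If dropout was added as n × 1.2 instead, 44 per arm gives 52.8, rounded up to 53, and SD = 5.17 (t-test 5.11).

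The total is thus consistent with an SD of about 5.0 to 5.2. That SD is an inference, not a figure from the article. I use 5.05 below.

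**3. Reading A: any of three visits, each at .05, without correction**

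With three independent tests the chance of at least one false positive is 1 − 0.95³ = 14.3%. Visits in the same patients are correlated. Simulating three equally correlated null test statistics (1,000,000 draws) and counting any |Z| > 1.96 gives:

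| Assumed correlation | 0.4 | 0.5 | 0.6 | 0.7 | 0.8 |
|---|---|---|---|---|---|
| Family-wise error | 13.1% | 12.5% | 11.8% | 10.9% | 9.8% |

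The correlations are assumptions; the article gives none.

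**4. Reading B: Bonferroni over the three visits**

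- The level per visit is .05 / 3 = .0167, with critical value 2.394. Family-wise error is at most 5%.
- Power per visit with 42 evaluable per arm and SD 5.05 is Φ(3.2415 − 2.394) = Φ(0.848) = 80%.
- Restoring 90% needs 42 × (2.394 + 1.282)² / (1.960 + 1.282)² = 54 evaluable per arm. Then 54 / 0.8 = 67.5, rounded up to 68 per arm, or 136 in total.

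**5. One named visit at .05**

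If the difference of 3.57 and an SD of about 5.05 hold at that visit, 42 evaluable per arm gives 90% power and the total stays at 106.

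**The case against.** The strongest reply is that the plan is more settled than this suggests.

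- **The model is named.** The Statistical Analysis section assigns ANCOVA to the primary outcome. A mixed model for the time course alongside it is a coherent plan. This stands: a reader might infer that no primary model was chosen, and the text does not support that. What is open is the visit, and whether the Bonferroni rule reaches the primary test.
- **Multiplicity is addressed.** If the Bonferroni sentence covers the ODI contrasts, family-wise error is at most 5%. This also stands. A reader might conclude that the 5% error rate fails outright. It fails only if ANCOVA is run at several visits outside that rule, and the article does not say that it will be.
- **Week 4 is implied.** The Outcome section puts the full set of measurements at week 4, and Table 1 labels weeks 8 and 16 as follow-up. This is a fair hint, and it makes week 4 the natural candidate. It is not a declaration, and the sizing text points to another week.
- **Week 6 may be harmless to the number.** The arithmetic depends on the difference, SD, level and dropout, not on the label of the visit. True, so the total of 106 is not shown to be wrong. But the article gives no reason why the assumed difference applies at any scheduled visit.

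The analysis plan might name the visit. That would not remove the contradiction between the sizing text and the schedule, which stands in the article itself.

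**Conclusion.** The point holds as an internal contradiction with an open consequence. The stated 90% power refers to a week at which ODI is not measured, and the primary ANCOVA has no defined time point.

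The size depends on the reading. Free choice among three uncorrected visits would give a family-wise error of about 10% to 13%, at assumed correlations of 0.8 to 0.4. Bonferroni over all three keeps error at or below 5% but leaves about 80% power per visit, given 42 evaluable per arm and the back-solved SD of about 5.05. Thus one reading departs from the stated level and the other from the stated power. A single named visit preserves both, provided that the assumed difference and SD hold there.

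The documents do not support replacing ANCOVA with the mixed model for the primary test. That would be a preference, since nothing shows the stated ANCOVA to be wrong.

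**What to change.** - **Primary endpoint.** Name one scheduled visit as the single primary endpoint. Week 4 is the natural candidate: it is the end of the intervention and the only post-baseline visit at which every listed outcome is measured.
- **Primary test.** Test it once, at two-sided .05, with the stated baseline-adjusted ANCOVA.
- **Other visits.** Make the other two ODI visits secondary, under the mixed model, and say that the Bonferroni rule applies there and not to the primary test.
- **Sample size text.** Replace week 6 with the named visit. State the SD, and say why the 3.57-point difference and that SD apply at this visit; otherwise restate the power. Changing the week alone would only relabel the assumption.

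The cost is wording in three sections and a dated registry update. No new data are needed, and the total stays at 106 if the assumptions carry over.

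Timing matters. The article reports all 106 participants recruited by August 2024 and analysis not begun, yet it expected publication in January 2025 and is itself dated May 2025. Whether the data are still blinded cannot be told from it. If they are, make the change before unblinding. If not, disclose openly when and how the primary visit was chosen.

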### Eligibility Criteria

#### Inclusion Criteria

The inclusion criteria are (1) the duration of CLBP is at least 3 months [21], and CLBP can be accompanied by numbness and weakness in the lower limbs; (2) computed tomography or magnetic resonance imaging showing lumbar disc herniation; (3) age between 20 and 60 years, regardless of gender; (4) NRS≥3 points and persistent low back pain (LBP) for more than 12 weeks; (5) those who have not received any other treatment regimen regarding lumbar disc herniation within the last 1 month; (6) no long-term exercise training in the last 3 months, including swimming, jogging, and yoga; and (7) voluntarily participate in this trial and sign an informed consent form.

#### Exclusion Criteria

The exclusion criteria are (1) combined with other major lumbar diseases, such as tumors and tuberculosis; (2) history of spinal surgery within 1 year; (3) those who are scheduled to undergo lumbar surgery in the next 3 months or who have plans to go out for a long period; (4) patients with severe mental system disorders (eg, schizophrenia, bipolar disorder, and major depression); and (5) pregnant or lactating women.

#### Randomization

This trial used computer-generated block randomization with a fixed block size of 6 to ensure balanced group allocation. The intervention is unified after the block is full. Randomization sequences were securely stored in sequentially numbered, opaque, sealed envelopes to maintain allocation concealment. These envelopes were managed by an independent staff member not involved in trial procedures or participant assessments. Envelopes were opened sequentially after participant enrollment was formally confirmed, strictly following the order of study identification numbers assigned at recruitment. Each enrolled participant received a unique study identifier linked to their randomization group, ensuring traceability while preserving blinding integrity throughout this trial.

#### Blinding

Participants and therapists will not be blinded due to differences in treatment methods. Assessors, data managers, and analysts will not be aware of the group assignments in the outcome evaluation process and data analysis to reduce the risk of bias.

#### Interventions

In Chinese hospitals, manipulative therapy interventions are the first choice for patients with CLBP; therefore, manipulative therapy was chosen as the basic treatment protocol before randomization. It is administered by licensed doctors who have a minimum of 5 years of clinical experience in treating LBP. They have extensive experience in practicing manipulative therapy. In a previous study [22-24], we provided a detailed description of the manipulative therapy technique applied to CLBP. A similar technique will be used in this trial. A complete manipulative therapy intervention will have a duration of 15 minutes. Specifically, kneading and rolling techniques will be used to relax the muscles in the patient’s lower back. Palm root pressure was applied to the lower back muscles of patients with LBP, and pressure was applied along the erector spinae muscle from top to bottom. The pressure was applied for 10 minutes, 80-100 times per minute.

Once all patients were enrolled, baseline data were collected, and baseline information such as disease and age was recorded on the envelope to eliminate baseline imbalance and other factors in the randomization of blocks. After the manipulative therapy, all the patients will be randomly divided into 2 groups. Participants will receive 2 treatments every week for a total of 4 weeks. The teacher must pass clinical tests to ensure consistency in every treatment for all patients. At the same time, the participants may continue to take their usual pain relief medication, such as nonsteroidal anti-inflammatory drugs. Changes in dosage should be recorded on the case report form (CRF).

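### Recording age and disease on envelopes opened in strict ID order cannot remove baseline imbalance, and the article gives two incompatible accounts of when allocation took place

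*Protocol article*

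**What the plan says.** All locations are in the protocol article.

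- **Randomization, method.** The trial used "computer-generated block randomization with a fixed block size of 6 to ensure balanced group allocation". No stratification factor and no minimisation is named.
- **Randomization, order.** Envelopes were opened one after another once enrolment was confirmed, "strictly following the order of study identification numbers assigned at recruitment".
- **Randomization, safeguards.** The list was kept in numbered envelopes that were sealed and opaque. On custody the article adds: "These envelopes were managed by an independent staff member not involved in trial procedures or participant assessments".
- **Randomization, batching.** "The intervention is unified after the block is full". The article does not explain this sentence.
- **Interventions.** After stating that all patients had been enrolled and baseline data collected, the article says that "baseline information such as disease and age was recorded on the envelope to eliminate baseline imbalance and other factors in the randomization of blocks". It then says that all patients are divided into two groups after the manual therapy.
- **Study Design.** One centre, with allocation "at a 1:1 ratio after receiving TCMT".
- **Blinding.** Participants and therapists are not blinded.
- **Statistical Analysis.** The primary outcome is analysed by ANCOVA adjusted for baseline. The mixed model for repeated outcomes also adjusts for age and gender.

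**The concern.** The Interventions section credits the allocation with a property that the procedure in the Randomization section does not have. A pre-generated list in permuted blocks, opened in a fixed order, takes no account of who the next participant is. It keeps the arm sizes close. It does nothing for age or disease beyond what simple chance does.

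So only one of two things can be true. Either the notes had no role in allocation and the balancing claim is wrong, or they had a role and the description of sequential, concealed opening is wrong. A reader cannot tell which. The second possibility would change what kind of randomisation this was and how it should be analysed.

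The timing adds to the doubt. The Randomization section implies that each participant was allocated after his or her own enrolment was confirmed. The Interventions section reads as if the whole sample was enrolled, documented and then divided.

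What is at stake is whether the report describes its randomisation truthfully, and whether the primary analysis leans on a balance that was never built in.

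**Working it through.** The article gives no figure for covariate balance or for predictability, so there is nothing of its own to reproduce on this point. The inputs taken from it are block size 6 (Randomization), ratio 1:1 and one centre (Study Design), and 53 per arm, 106 in total (Abstract).

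**1. Can the notes balance anything?**

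| Case | Effect of notes on allocation | Consequence |
|---|---|---|
| Envelopes opened strictly in ID order | None | The balancing claim is false |
| Notes decide which envelope is used, or in what order | Some | Opening is not strictly sequential, and the description of concealed allocation no longer holds |

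No third case is compatible with both sections.

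**2. How much chance imbalance remains?** With allocation independent of baseline and 53 per arm:
- Continuous factor (such as age), in SD units: 1.96 × √(2/53) = ±0.38 SD.
- Binary factor at an assumed prevalence of 50%: 1.96 × √(2 × 0.25/53) = ±0.19, or about 19 percentage points.

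These are the 95% ranges with or without notes on the envelopes.

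**3. How predictable is a fixed block of 6?** Assume that the enroller knows the block size and every earlier allocation in the block. There are C(6,3) = 20 equally likely sequences.
- Chance that a position is certain in advance: 0 at positions 1 to 3, 0.10 at position 4, 0.40 at position 5 and 1 at position 6. The sum is 1.5 of 6, or 25%.
- Chance that the best guess is right, by position: 0.5, 0.6, 0.6, 0.7, 0.7, 1.0. The sum is 4.1 of 6, or 68.3%, against 50% without restriction.

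If either piece of knowledge is missing, the figures are lower. If allocations were disclosed only when a block was full, the predictability falls or disappears.

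**4. What could a selection-bias check show?** 106 = 17 × 6 + 4. Expected forced allocations: 17 × 1.5 + 0.10 = 25.6, or 12.8 per arm by symmetry. For baseline ODI compared between those forced to one arm and those forced to the other, the 95% half-width is about 1.96 × √(2/12.8) = 0.77 SD. Only strong steering would be visible.

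**The case against.** Several stronger readings are tempting, and the documents do not support them.

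- **That writing on the envelopes weakened concealment.** Details on the outside of a sealed, opaque envelope do not reveal its contents. Written before opening, they can guard against swapping. The article also reports an independent custodian and opening only after confirmed enrolment.
- **That allocation was in fact predicted.** The 25% and 68% are worst-case figures. Nothing says that enrollers knew the block size or the earlier allocations, or that the unblinded therapists enrolled anyone. The article giving the block size appeared in May 2025, after all 106 had been recruited by August 2024. The unexplained sentence about full blocks may even mean that disclosure was batched.
- **That age imbalance would bias the result.** Chance imbalance under randomisation is already reflected in the confidence interval and P value. The planned mixed model also covers ODI over time with age and gender adjustment.
- **That the unfilled last block matters.** With four participants in it, the split is 53:53 with probability 0.60 and otherwise 54:52. That has no material effect on power or bias.

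One could also say that the Interventions sentence is loose wording, meaning each patient rather than all patients, and an audit record rather than a balancing device. That may be so, but the article states a balancing purpose. These objections narrow the point; they do not remove the contradiction.

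**Conclusion.** The claim that the envelope notes eliminate baseline imbalance cannot stand beside the procedure in the Randomization section. The two sections also conflict on whether allocation ran participant by participant or after everyone was enrolled. This conclusion rests on the text alone and needs no outside figure.

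If the notes played no part, the consequence is a false statement about the design. Ordinary chance imbalance remains: about ±0.38 SD for a continuous factor, and about ±19 percentage points for a binary one at an assumed 50% prevalence. If they did play a part, the randomisation needs a different description and possibly a different analysis. The documents do not show that this happened, and they show no breach of concealment.

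The fixed block of 6 in one centre with open treatment is a limitation that depends on what enrollers knew, which the article does not say. The point should be corrected before analysis; it does not by itself undermine the trial.

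**What to change.** 1. **Balancing claim.** Delete it. State what the notes were for (for example, an audit record) and that they did not influence allocation. If they did, describe the procedure actually used and analyse accordingly.
2. **Timing.** Reconcile the Randomization and Interventions sections on when envelopes were opened relative to enrolment, and explain the sentence about full blocks.
3. **Primary ANCOVA.** Add age and gender to baseline ODI, for precision and consistency with the mixed model, not to remove bias. With all 106 analysed, residual degrees of freedom go from 106 − 3 = 103 to 101. The article says that analysis has not begun. If it has since begun, label the addition as made afterwards.
4. **Fixed block.** Report it as a limitation with its conditions: 25% certain and 68% guessable only if block size and all earlier allocations were known, and less or none if disclosure waited for a full block.
5. **Optional check.** If selection bias is examined, compare baseline ODI between participants forced to one arm and those forced to the other, under coded labels. Pooling all forced allocations against the rest could cancel opposite shifts. State that the check is weak, with about 13 per arm expected.

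The cost is corrected wording in two sections, two covariates already named in the plan, and at most one short additional analysis.
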